#### **5.6.4 Labeling**

Each aspirin, clopidogrel or placebo bottle will be labeled in black ink. On this label the protocol number, blinded batch number, container number, blinded drug name, tablet quantity, storage conditions, directions for use and route of administration will be indicated.

At the study site, the investigational product should be stored in a secure area according to local regulations. It is the responsibility of the investigator to ensure that the investigational product is only dispensed to study subjects. The investigational product must be dispensed only from official study sites by authorized personnel according to local regulations.

The storage conditions for the subjects to follow will be included in the labeling on the bottles.

### **5.7 Concomitant and post-study treatment**

There are no protocol specific concomitant treatments. After study completion, the physician will determine the ongoing medical treatment for each subject. These medications are open-label, and are available on their local sites (no more available for free).

### **5.8 Treatment compliance**

Study drug compliance will be assessed using manual pill count at the 12-month in-person follow-up visit. Reconciliation between the quantity of shipped study drugs versus the allocation of study drugs via EDC and versus distribution of study drug to subject will be monitored and reconciled by investigators and trial monitors.

### **5.9 Discontinuation of study medication**

#### **5.9.1 Temporary discontinuation from study medication**

In the event such as surgery or other invasive procedures that a subject is temporarily discontinued from study drugs or need a replacement of the blinded-label study drugs to open-label antiplatelet drugs <7 days according to local standard of care, subjects should be considered, where possible, for eligibility to resume blinded-label study drug under the judgement of treating physicians.

Details on the date, duration and cause of each temporary discontinuation of study drugs should be recorded in full in the appropriate section of the EDC.

### **5.9.2 Permanent discontinuation from study medication due to reasons below:**

- Patient decision. The patient is at any time free to discontinue treatment, without prejudice to further treatment.
- Investigator's decision:
  - 1) Incorrectly enrolled patient in whom the inclusion/exclusion criteria violation would put the patient at undue risk.
  - 2) Investigators judge that due to adverse events related to any kind of study drug, continuous administration of this study drug would put the patient at undue risk.

Details on the date, duration and cause of each permanent discontinuation of study drugs should be fully recorded into the appropriate section of the EDC. When any of the study drugs are permanently discontinued, further antiplatelet therapy should be given to the subject according to attending physician's discretion. Any remaining study drugs should be returned to the local research site at the next scheduled follow-up visit. Although these subjects are no longer receiving any study drug, they should also be followed up until 12 months. Patients who permanently discontinue study drugs after randomization are still required to undergo AMCE examination, and investigators are required to withdraw study drugs from patients after discontinuation. Patients who permanently discontinue study drugs before randomization only needed to be followed up by telephone at 12 months.

## **5.10 Withdrawal from study**

Each enrolled subject shall remain in the trial until completion of the required follow-up period. However, a subject's participation in any clinical trial is voluntary and the subject has the right to withdraw at any time without penalty or loss of benefit. Conceivable reasons for discontinuation may include, but not be limited to, the following:

- Subject voluntary withdrawal
- Subject withdrawal by physician as clinically indicated
- Subject lost-to follow-up

The reason for subject discontinuation must be documented on the CRF and source documents. The principal investigators must also report all subject discontinuations to their Ethical Committee as defined by their sites' procedure. All data from

evaluations and treatments performed prior to the withdrawal should be documented on the CRFs. Source documents that pre-date the withdrawal should be submitted as required by the protocol. No data that post-dates the withdrawal will be collected.

Once a subject has withdrawn from the trial, no further follow-up contact will be performed. However, vital status may be obtained from public records. Medical therapy after stopping the study will be as prescribed by the subject's physician.

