## 12.3 Determination of sample size

The cumulative incidence of the primary endpoint of gastric or small intestinal mucosal lesions within 12 months is estimated to be 47% in patients who received 12 months of DAPT and 30% in those treated with either aspirin or clopidogrel monotherapy beginning at 6 months after enrollment. With a 2:1 ratio in patients treated with either aspirin or clopidogrel monotherapy (the sum of aspirin monotherapy group and clopidogrel monotherapy group) after 6-month DAPT versus DAPT for 12 months, 384 evaluable patients (256 and 128 respectively) provide 90% power to detect a 17% absolute risk reduction (36% relative risk reduction) with a 2-sided type I error of 0.05. Assuming 20% loss of evaluable primary endpoint outcome assessments due to patient withdrawal, loss to follow-up between 6 and 12 months or suboptimal AMCE visualization of the GI tract at 12 months, 480 patients are planned to be randomized. Assuming that an additional 10% of enrolled patients will not be randomized at 6 months because of adverse clinical events, non-compliance with antiplatelet therapy, lost to follow-up or withdrawal, 534 patients is required to be initially planned to be enrolled after baseline screening. Finally, assuming that 10% of patients who undergo a screening AMCE examination will be excluded due to unavailable valid image (or definite ulceration and active bleeding), therefore a total of 593 patients is initially planned to be consented and undergo the screening AMCE examination.

Among the first 200 patients enrolled, ~25% had gastrointestinal injury at baseline by screening AMCE (despite clinically absent bleeding or gastrointestinal complaints). Of those who passed the initial exam, only ~65% were eligible for randomization; 17% of patients were noncompliant with the 6-month repeat AMCE exam, and new gastrointestinal ulceration or bleeding was found on the 6-month AMCE examination in 18% of patients. The study sample size was adjusted accordingly so 1000 patients will be screened by AMCE at baseline, with 750 patients enrolled and followed to the 6-month randomization eligibility period to achieve the 480 patients randomized goal.

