## **6 Analysis sets**

### **6.1 Full analysis set (FAS)**

All patients who have been randomized to study treatment will be included irrespective of their protocol adherence and continued participation in the study. Patients will be analysed according to their randomized study drug assignment (not to which treatment they actually received) irrespective of whether the event occurred before or following discontinuation of study drug. Patients who withdraw consent to participate in the study (or are lost to follow-up) will be included up to the date of

their study termination except for vital status known through public records (for use in the analyses of deaths). All primary, secondary, and exploratory efficacy variables will be analyzed using the FAS. The primary endpoint of gastric or intestinal mucosal injury will be analyzed in a modified intention to treat (mITT) population, (i.e., patients with valid primary endpoint results). Unless otherwise stated, the FAS will be considered the primary analysis set for the primary and secondary variables and for the exploratory variables.

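### Protocol 5.10 stops data collection and contact after a physician's withdrawal or loss to follow-up, as if consent had been withdrawn, and is not reconciled with 5.9.2, 5.5.2 or Appendix 18.2(4)

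*Supplement*

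**What the plan says.** Protocol v1.4, section 5.10, opens by saying that enrolled subjects stay in the trial until follow-up is complete. It then gives three example reasons for leaving: voluntary withdrawal, "Subject withdrawal by physician as clinically indicated", and loss to follow-up. No criteria are attached to the second. The consequence is the same for all three: data from before the exit are documented, nothing later is collected, and "Once a subject has withdrawn from the trial, no further follow-up contact will be performed". Vital status may still be taken from public records.

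Section 5.9.2 deals with permanent discontinuation of study drug. One of its grounds is the investigator's judgement that a drug-related adverse event makes continuing unduly risky. For these patients, "Although these subjects are no longer receiving any study drug, they should also be followed up until 12 months", and those already randomized still have AMCE.

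Section 5.5.2 keeps 12-month clinical follow-up and AMCE for unblinded patients. Appendix 18.2(4) keeps a patient who bleeds after randomization in the study, with clinical follow-up to 12 months but no AMCE.

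SAP 6.1 defines the full analysis set: "All patients who have been randomized to study treatment will be included irrespective of their protocol adherence and continued participation in the study". It includes patients who withdraw consent or are lost up to the date they leave, and analyses the primary endpoint in those with a valid result (mITT). SAP 8 adds complete-case, best-case, worst-case and tipping-point analyses.

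**The concern.** Stopping study drug and leaving the study are different acts, and 5.9.2 keeps them apart. Section 5.10 blurs them by giving the physician an undefined power to end participation on clinical grounds, with the same consequence as a patient's refusal. A site facing a drug-related adverse event can follow either section. Under 5.9.2 the outcome is kept; under 5.10 it is given up. Listing loss to follow-up as a withdrawal also means that, read strictly, attempts to re-contact an unreachable patient cease.

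A clinical decision to take someone out is unlikely to be independent of bleeding, ischaemic events or mucosal injury. Missing outcomes that arise this way may be informative, and they are avoidable because the patient has not declined to be followed.

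**Working it through.** **1. The rules side by side (protocol v1.4)**

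| Situation after randomization | Section | Clinical follow-up to month 12 | 12-month AMCE |
|---|---|---|---|
| Investigator stops drug for an adverse event | 5.9.2 | Yes | Yes |
| Blind broken | 5.5.2 | Yes | Yes |
| GI bleeding | Appendix 18.2(4) | Yes | No |
| Physician withdraws the subject on clinical grounds | 5.10 | No | No |
| Lost to follow-up | 5.10 | No contact | No |
| Subject withdraws voluntarily | 5.10 | No | No |

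The broad ground in 5.10 can take in the adverse-event ground in 5.9.2, and no section states precedence. The AMCE column also differs between 18.2(4) and the two rows above it, so a bleeding patient who is unblinded falls under two different instructions.

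**2. What is lost when 5.10 is followed**

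- *Primary endpoint.* Protocol 11.1 and SAP 4.1 accept bleeding-driven AMCE or gastroscopy that finds new lesions, whenever it occurs in the study. SAP 4.1 also accepts new lesions at the 6-month AMCE if the third examination is not done. Section 5.10 keeps data from before the exit. The loss is therefore limited to injury not yet detected when the patient leaves.
- *Clinical endpoints.* Later bleeding, TLF, NACE, stent thrombosis and MACCE are all unobserved.

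**3. What the SAP does with these patients**

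SAP 6.1 (inclusion up to exit) and SAP 9.3.2 (censoring at last contact) name withdrawal of consent and loss to follow-up. Neither names withdrawal by a physician. The SAP 8 scenarios are written for the mucosal-injury outcome and not for the time-to-event endpoints.

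**4. What the 20% allowance and SAP 8 can and cannot do**

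Inputs from protocol 12.3: the incidence "is estimated to be 47% in patients who received 12 months of DAPT and 30% in those treated with" monotherapy, tested "with a 2-sided type I error of 0.05"; "384 evaluable patients (256 and 128 respectively) provide 90% power"; and "Assuming 20% loss of evaluable primary endpoint outcome assessments due to patient withdrawal" among other causes.

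The plan's size reproduces. With pooled variance and 2:1 allocation, the average rate is (0.47 + 2 × 0.30)/3 = 0.3567, and

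n(DAPT) = [1.960 × √(1.5 × 0.3567 × 0.6433) + 1.282 × √(0.47 × 0.53 + 0.30 × 0.70/2)]² / 0.17² = 127.

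That gives 127 + 254 = 381, against 384 stated. Then 384/0.8 = 480, as stated. The allowance restores the number of evaluable patients. It does not make the patients who remain representative.

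SAP 8 bounds, assuming the planned rates in those observed and 20% missing in each arm (160 and 320 randomized; 32 and 64 missing; 128 × 0.47 = 60.16 and 256 × 0.30 = 76.8 events):

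- Best case: DAPT (60.16 + 32)/160 = 57.6%; monotherapy 76.8/320 = 24.0%.
- Worst case: DAPT 60.16/160 = 37.6%; monotherapy (76.8 + 64)/320 = 44.0%.

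These bounds cover missing results from every cause at the full allowance; they do not estimate the effect of 5.10. They show that sensitivity analysis can only bracket missing outcomes. At the planned 20% the bracket is wide enough to reverse the direction of effect.

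**The case against.** The best defence is that the rest of the protocol already narrows 5.10. Its first sentence expects subjects to stay in, and 5.9.2 and 5.10 formally govern different acts. The specific rules in 5.5.2 and 18.2(4) cover unblinding and bleeding. Loss to follow-up is a fact and not a permission, so listing it need not stop a site from trying again. SAP 8 plans for missing results.

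Much of this stands, and it rules out three stronger readings that a reader might infer:

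- *That patients who bleed or are found injured simply disappear from the primary analysis.* Appendix 18.2(4) keeps patients who bleed after randomization in the study, and endoscopy-confirmed new lesions are already valid results.
- *That the effect is biased towards no difference, with a calculable loss of power.* The documents give no rate of physician withdrawal. Any figure would need invented rates and the assumption that every withdrawn patient is a lost primary event. It would also have to avoid deducting withdrawals twice, since the 384 is already net of the 20% allowance. Nor is the direction settled: protocol 1.3 names thrombotic risk on monotherapy as well as bleeding risk on DAPT, so clinically driven exits could lean either way.
- *That 5.10 contradicts the SAP's full analysis set.* It removes nobody from that set, which allows for truncated follow-up, and the primary endpoint is analysed in mITT.

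The defence does not answer the overlap. No text gives precedence to the specific rules, the physician's ground in 5.10 has no limits, and the ban on contact is explicit.

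**Conclusion.** The point holds as an unresolved overlap that permits avoidable loss of outcomes. Section 5.10 attaches the consequence of withdrawn consent to two situations in which consent has not been withdrawn, while 5.9.2, 5.5.2 and 18.2(4) point towards continued follow-up. The loss falls on undetected injury and on later clinical events. It may be related to outcome, but neither its size nor its direction can be derived from the documents. This conclusion assumes only that some sites would apply 5.10 as written. It disputes no sample-size or power figure in the plan.

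**What to change.** In 5.10, state that only the subject's own withdrawal of consent ends data collection and contact. After a physician's decision, outcome follow-up continues to month 12 as in 5.9.2. Patients who cannot be reached continue to be contacted to month 12.

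Reconcile 5.10 with 5.9.2, 5.5.2 and Appendix 18.2, and say which section governs. That includes settling whether the 12-month AMCE applies in each situation, which is a clinical rule for the investigators and is not prescribed here. The early exits in 5.1 and 5.4 should be checked against the same statement, and SAP 6.1 and 9.3.2 should say how any remaining physician-decided exits are handled.

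The cost is a short clarification, a note to sites and a few extra contacts. No treatment decision and no planned number changes.

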## **6. COLLECTION OF STUDY VARIABLES**

### **6.1 Recording of data**

The Investigator is responsible for maintaining complete and accurate documentation of the trial including but not limited to medical records, trial progress records, laboratory results, case report forms, signed informed consent forms, investigational product accountability records, correspondence with the EC or trial monitors, adverse event reports, and information regarding subject discontinuations.

The Investigator is required to maintain information in the subject's medical records which documents and corroborates data entered in the case report forms. As a minimum the subject record should contain:

- Medical history/physical exam documenting that subject meets inclusion/exclusion criteria
- Documentation of subject's consent and subject ID number in the trial
- Dated and signed notes from each subject visit
- Adverse events reported and their resolution or lack thereof including supporting documents such as hospital records, discharge summaries, catheterization reports, ECGs, etc.
- Record of protocol required medications during the trial
- Record of the subject's condition upon completion of or withdrawal from the trial

### **6.2 Data collection at enrollment and follow-up**

Data collection commences after the subject has provided informed consent. Data collection including subject demographic information, laboratory tests, and procedural data, and AMCE examination data as well as follow-up visits or telephone contacts will be conducted by an Investigator or site coordinator who has been trained on the

protocol and Case Report Forms (CRF).

Data required for analysis will be obtained as outlined in Table 2.

**Table 2 schedule of data collection**

|                                                                                        | Screening for Enrollment | Standard DAPT and randomization | After randomization       |
|----------------------------------------------------------------------------------------|--------------------------|---------------------------------|---------------------------|
| Study procedures                                                                       | After PCI                | Until 6 months after PCI        | Until 12 months after PCI |
| Follow-Up                                                                              | Visit 1                  | Visit 2                         | Visit 3                   |
| Window Period                                                                          | 0-7 days                 | ±7 days                         | ±14 days                  |
| Eligibility Criteria                                                                   | X                        |                                 |                           |
| Patient Informed Consent                                                               | X                        |                                 |                           |
| Withdrawal                                                                             | X                        | X                               | X                         |
| Medical History/ Demographics                                                          | X                        |                                 |                           |
| Previous Medical History                                                               | X                        |                                 |                           |
| Vital Signs                                                                            | X                        | X                               | X                         |
| Height and Weight                                                                      | X                        |                                 |                           |
| Physical Examination                                                                   | X                        |                                 |                           |
| Cardiac Markers (including TnT or TNI/CK/CK-MB)                                        | X                        |                                 |                           |
| Blood Routine Test  (RBC/WBC/HGB/PLT)                                      | X                        | X                               | X                         |
| Coagulation Function Test (PT/APTT/FIB)                                                | X                        |                                 |                           |
| Fecal Occult Blood Test                                                    | X                        | X                               | X                         |
| Platelet Aggregation Test  (light transmission aggregometry and VerifyNow) | X                        | X                               | X                         |
| HP Breath Test                                                                         | X                        |                                 |                           |
| 12-Leads ECG                                                                           | X                        |                                 |                           |
| AMCE Examination                                                                       | X                        | X                               | X                         |
| Drug Distribution/Recycling                                                            | X                        | X                               | X                         |
| Concomitant Medications                                                                | X                        | X                               | X                         |
| Adverse Events                                                                         | X                        | X                               | X                         |

1: one time per two months; 2: 34 patients per group in the principal research site

6-month visit: Each enrolled subject will be followed with an in-clinic face-to-face visit at 6 months after enrollment. Screening should be conducted before the 6-month face-to-face visit, subjects who are not eligible for randomization will not be required to complete the 6-month face-to-face visit.

12-month visit: Randomized subjects will return for the final in-clinic additional in-clinic face-to-face visits at 12 months after enrollment. Vital status of subjects who

did not meet eligibility for randomization can be obtained from medical records or public records at 12 months after enrollment.

### **6.2.1 Enrollment procedures**

For patients who meet all inclusion criteria and do not meet any exclusion criteria, the investigator or designee will:

- Obtain written informed consent
- Obtain a complete demographic data, medical history, physical inspection information (including blood pressure, pulse, height, weight and ECG), and lab values including hemoglobin and creatinine
- Conduct the initial AMCE examination to determine baseline characteristics of gastrointestinal mucosa
- Review concomitant medications taken within the last 30 days
- Instruct the subject to notify the investigator of any occurrence of adverse events
- Schedule next clinic visit at 6 months, and instruct patients to administer DAPT (aspirin plus clopidogrel) during the first 6 months after PCI

